#### Effectiveness secondary parameters

The number of days until participants’ return to work (either full or partial) assessed at 12 months will be analysed using the Kaplan-Meier survival method, and differences between groups will be tested with the log-rank test. Patients who dropped out of the study will be censored. If statistically significant differences in prognostic characteristics between the intervention and the control group are found at baseline, a Cox regression analysis will be performed including those prognostic parameters.

A longitudinal multilevel analysis will be used to examine differences between intervention and the control group with regard to improvement of work ability, work limitations, quality of work life and quality of life.

A cut-off score of ≥6 on the subscale need for recovery of the VBBA will be used to divide the group of participants who returned to work without extensive need for recovery versus the group of participants who returned to work with an extensive need for recovery plus the participants who did not return to work. The number of days until participants’ return to work without extensive need for recovery at 12 months will be analysed using the Kaplan-Meier survival method, and differences between groups will be tested with the log-rank test. If statistically significant differences in prognostic characteristics between the intervention and the control group are found at baseline, a Cox regression analysis will be performed including those prognostic parameters.

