**Methods:**

We designed a multi-centre randomised controlled trial with a follow-up of 12 months. Patients who have paid employment at the time of diagnosis, are on sick leave and are between 18–62 years old will be eligible to participate. After patients have signed the informed consent form and filled in the baseline questionnaire, they are randomly allocated to either the nurse-led, stepped-care, e-health intervention called Cancer@Work, or care as usual. The primary outcome is sustainable return to work. Secondary outcomes are sick leave days, work ability, work functioning, quality of life, quality of working life and time from initial sick leave to full return to work without extensive need for recovery. The feasibility of the Cancer@Work intervention and direct and indirect costs will be determined. Outcomes will be assessed by questionnaires at 3, 6, 9 and 12 months of follow-up.

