### Sample size

On average, we will include cancer patients at 6 weeks or 42 days after diagnosis, and the follow-up time for the primary outcome return to work will be 12 months after inclusion, hence 12 months and 42 days after diagnosis. Earlier studies in our hospital showed that return to work for patients with various cancer types was 64 % at 12 months of follow-up from diagnosis [28]. In addition, earlier studies in our hospital showed that return to work in the first 42 days is around 8 % [28]. Therefore, the return to work for the control group was set at 64 % + 8 % = 72 %. In a study of Nieuwenhuijsen et al. [29], an intervention group of 35 radiotherapy patients received a supportive work-related intervention in a hospital. Time between diagnosis and the end of treatment was a median 42 days. Return to work was measured between the end of treatment and work resumption and was 89 % after 12 months. Therefore, the return to work for the intervention group in our intervention was also set at 89 %.

Based on our earlier studies on consecutive cancer patients, a power analysis indicated that we should include a total of 170 patients with a follow-up of 1 year after inclusion to indicate a difference of 89 % return to work in the intervention group versus a 72 % return-to-work rate in the control group, with a power of 80 % and *p* < 0.05. Accounting for 10 % loss to follow-up, 190 patients should be included.

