### Assessment of the outcomes

Data will be both self-reported and collected by recording use of the Cancer@Work intervention by participants and recording the content of the assignments made by participants. The self-reported outcomes will be assessed at baseline and at 3, 6, 9 and 12 months of follow-up using questionnaires that will be completed by participants randomised to the intervention group and control group with online software. All participants will receive an email with a link to complete the questionnaire online if they indicate to prefer questionnaires online; otherwise, they will receive paper questionnaires. Completing a questionnaire will take approximately 30 minutes.

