#### Effect evaluation

The primary outcome of sustainable return to work is measured as any return to work (yes/no) at follow-up independent to the number of contract hours which is sustained for at least 4 consecutive weeks without recurrent sick leave. Return to work is either partial return to work (working a part of contract hours) or full return to work (working all contract hours).

The secondary outcomes are full return to work (yes/no) at follow-up defined as working the hours stated in the work contract, time to any (either partial or full) return to work in days from the first day of sick leave to the date of any return to work and time to return to work in days from the first day of sick leave to the date of full return to work. These return-to-work measures must be sustained for at least 4 consecutive weeks. Furthermore, secondary outcome measures are work ability using the first three questions of the Work Ability Index (WAI) [34], work functioning using the Work Limitations Questionnaire (WLQ) [35, 36], quality of life using the SF-12 [37], quality of work life using the QWLQ-CS (De Jong et al. in preparation) [38] and the time from initial sick leave to full return to work without extensive need for recovery using a subscale of the ‘perception and assessment of work questionnaire’ (VBBA) [39].

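### Work limitations and quality of work life are compared between arms as ITT improvement, but at-work scores come only from patients selected after randomisation by what is essentially the primary outcome

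*Protocol article*

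**What the plan says.** Under Effectiveness secondary parameters, the protocol article assigns one longitudinal multilevel analysis to four outcomes together. Its stated target is "differences between intervention and the control group with regard to improvement of work ability, work limitations, quality of work life and quality of life". The opening of Statistical analysis puts every analysis under the intention-to-treat principle.

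Effect evaluation names the instruments for the two scales at issue: "work functioning using the Work Limitations Questionnaire (WLQ") and "quality of work life using the QWLQ-CS".

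On work status at entry, the abstract describes the eligible group as "Patients who have paid employment at the time of diagnosis, are on sick leave". The Participants section does not repeat the sick-leave condition. Sample size reports from earlier hospital studies that "return to work in the first 42 days is around 8" per cent.

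Assessment of the outcomes says: "The self-reported outcomes will be assessed at baseline and at 3, 6, 9 and 12 months of follow-up using questionnaires". It does not say which scales a patient who is not working fills in, or how such a patient is scored.

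Two other places bear on the point. The Economic evaluation under Assessment of the outcomes costs absenteeism from sick-leave days and costs lost productivity separately, using the WLQ. Effectiveness secondary parameters treats need for recovery, another at-work measure, by grouping patients who did not return with those who returned in the unfavourable state, so that all randomised patients stay in that analysis.

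**The concern.** A patient on sick leave has no current work functioning or quality of work life. This causes two problems.

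- **Baseline.** If nearly everyone enters on sick leave, there is no starting value from which most patients can improve on these scales.
- **Follow-up.** A patient acquires an at-work score by going back to work. The intervention is designed to change exactly that, and it is essentially the primary outcome. If the intervention succeeds, the scored subsets in the two arms are no longer exchangeable: the intervention subset includes patients who would not have been at work under usual care.

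A multilevel model does not repair this. Likelihood-based handling of incomplete repeated measures covers scores that exist but were not recorded. The at-work score of someone not at work is undefined, not missing at random.

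At stake is what the trial can claim on two listed secondary outcomes. A difference, or its absence, would be presented as an ITT effect on functioning when part of it may reflect who got back to work.

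**Working it through.** **Inputs from the Sample size section.** Control return: "the return to work for the control group was set at 64 % + 8 % = 72" %. Intervention return: 89 %. Power 80 %, p < 0.05, 170 patients, 190 after 10 % loss.

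**1. Reproduce the plan's figure.** Two-sided test of two proportions, pooled variance under the null, no continuity correction, mean proportion 0.805:

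n per arm = [1.960 × √(2 × 0.805 × 0.195) + 0.842 × √(0.72 × 0.28 + 0.89 × 0.11)]² / 0.17² = (1.960 × 0.5603 + 0.842 × 0.5473)² / 0.0289 = 84.1, rounded up to 85.

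That gives 170 in total, as stated. 170 / 0.90 = 188.9, so 189 against the stated 190. The return rates below are therefore the ones the plan rests on.

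**2. Who has an at-work score at 12 months.** The planned return rates are taken as the share at work, which is an approximation.

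| | Control | Intervention |
|---|---|---|
| At work | 0.72 × 85 = 61.2 | 0.89 × 85 = 75.7 |
| Not at work | 0.28 × 85 = 23.8 | 0.11 × 85 = 9.4 |

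**3. Who has one at baseline.** Read with the abstract's sick-leave criterion, almost nobody. Read with the 8 % figure instead, about 0.08 × 95 = 7.6 per arm of the 190 enrolled. On either reading, change from baseline is undefined for most patients.

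**4. Possible size of the selection shift.** The intervention is assumed to change no individual's functioning. It is also assumed that nobody who would return under usual care fails to return under the intervention. The documents give no figure for how functioning relates to return, so a range is shown in two ways.

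*Strata.* Extra returners make up (0.89 − 0.72) / 0.89 = 0.191 of intervention patients at work. If they function g SD worse than the others, the shift is −0.191 × g:

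| g (assumed) | Shift |
|---|---|
| 0.25 | −0.05 SD |
| 0.5 | −0.10 SD |
| 1.0 | −0.19 SD |

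*Threshold model.* Functioning and propensity to return are bivariate normal with correlation ρ. The shift is ρ × [φ(t₁)/0.89 − φ(t₀)/0.72] = ρ × (0.211 − 0.468) = −0.256 × ρ:

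| ρ (assumed) | Shift |
|---|---|
| 0 | 0 |
| 0.2 | −0.05 SD |
| 0.3 | −0.08 SD |
| 0.5 | −0.13 SD |
| 0.7 | −0.18 SD |

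A negative ρ reverses the sign (+0.08 SD at ρ = −0.3). Simulation at ρ = 0.2, 0.3 and 0.5 gave the same values.

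**5. Scale.** With 61 and 76 scored patients, the difference detectable with 80 % power is (1.960 + 0.842) × √(1/61 + 1/76) = 2.802 × 0.172 = 0.48 SD. A shift of 0.05 to 0.19 SD is about 10 to 40 % of that.

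**6. What a composite would show.** Rank every non-worker below every worker, and let functioning among workers be identical in the two arms. The probability that an intervention patient ranks higher, counting ties as half, is 0.89 × 0.28 + 0.5 × (0.89 × 0.72 + 0.11 × 0.28) = 0.249 + 0.336 = 0.585, against 0.50 under no difference.

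**The case against.** The strongest reply is that the article never says only workers complete the two scales. Questionnaires go to all participants, and completion rules, recall periods and missing-data handling may stand in the instrument manuals, the full protocol or a SAP not shown here. It also does not say that improvement means change from baseline; a trajectory over follow-up is possible.

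Part of this stands. A reader might infer that the documents restrict the scales to patients at work, but they do not; that is an inference from the constructs. For the WLQ it is supported by the separate costing of absenteeism and WLQ productivity loss. For the QWLQ-CS it rests on what the scale sets out to measure. The reply does not remove the problem, however. If non-workers leave the scales blank, the comparison is among workers. If they answer, they cannot be describing current work.

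A reader might also infer that the planned comparison is biased against an intervention that works. The documents do not support that as a fact. It needs the extra returners to function worse than other workers, for which no figure is given, and it needs the intervention to keep nobody from returning. The Effectiveness section describes patients at high risk of not returning by low work ability, fatigue, depression and cognitive problems at work, which makes that direction plausible but does not establish it.

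Finally, the plan already has one secondary endpoint combining return with an at-work measure and keeping non-returners, namely return without extensive need for recovery. That softens the practical consequence but leaves the WLQ and QWLQ-CS undefined for patients not at work. The objection that a composite largely re-tests return to work is also fair, as step 6 of the working shows.

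**Conclusion.** The point holds for two of the four outcomes in the quoted sentence. For the WLQ and QWLQ-CS, a between-arm comparison of at-work scores conditions on an event after randomisation that treatment is meant to affect, so it is not an ITT comparison. This follows from the constructs and from the plan's own 72 % and 89 %, and needs no assumption about direction. Work ability and SF-12 are not affected.

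Size and direction are conditional: roughly 0.05 to 0.19 SD against the intervention under the assumptions in step 4, zero if functioning is unrelated to return, and reversed if the relation is negative. The shift is modest beside a detectable difference of about 0.48 SD, but it could hide part of a benefit or suggest a small harm. These are secondary outcomes.

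**What to change.** Before the data are analysed, split the sentence on the multilevel analysis in two.

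- **Work ability and SF-12:** keep the planned multilevel ITT comparison.
- **WLQ and QWLQ-CS:** state who completes them and how a patient not at work is handled. Do not analyse change from baseline. Report the workers-only comparison as descriptive, with the number at work in each arm at each assessment, and not as an ITT treatment effect.
- **Supporting analysis for these two scales:** include all randomised patients and keep non-returners in the unfavourable category, as the same section does for need for recovery. A rank analysis placing not working below any at-work score is one way, and it needs no cut-off.

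The cost is wording and one added analysis, with no new data. The drawback is that the supporting analysis mixes return with functioning. At the planned rates it would show a probability of about 0.585 even with identical functioning among workers. It must therefore be labelled and read as a combined outcome, beside the return rates and the descriptive workers-only scores, and not as an effect on functioning.

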#### Intermediate effect of the Cancer@Work intervention on self-management and work-related self-efficacy

The Cancer@Work intervention is a self-management intervention based on problem-solving techniques and cognitive behavioural techniques. The key mechanisms of the Cancer@Work intervention are therefore self-management skills and work-related self-efficacy. To measure this change in self-management skills, we will measure perceived confidence in own self-management skills on a visual analogue scale of 0 (no confidence) to 100 (high confidence). Work-related self-efficacy will be measured with the 11-item questionnaire ‘expectations regarding work functioning’ [43] with higher scores indicating more self-efficacy regarding work.

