### Statistical analysis

All analyses will be based on the intention-to-treat (ITT) principle. All baseline data and data regarding primary and secondary outcomes as well as data from the feasibility evaluation will be presented using descriptive statistics. Differences in baseline data between the intervention and control group will be assessed using Student’s *t* test for continuous data and the chi-squared test for categorical data.

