#### Intermediate effect of the Cancer@Work intervention on self-management skills and work-related self-efficacy

A longitudinal multilevel analysis will be used to examine differences between the intervention and the control group on self-management skills and work-related self-efficacy.

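### The multilevel models for the secondary and intermediate scores give the outcome's own baseline value no role as a covariate; read as change from baseline, they lose precision that adjustment would recover at no cost

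*Protocol article*

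**What the plan says.** All references are to the protocol article.

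- **Effectiveness secondary parameters** plans one longitudinal multilevel comparison of the arms for four outcomes, "with regard to improvement of work ability, work limitations, quality of work life and quality of life".
- **Intermediate effect on self-management skills and work-related self-efficacy (statistical analysis)** names the same type of model, for "differences between the intervention and the control group on self-management skills and work-related self-efficacy". The word improvement does not appear there. The corresponding section under outcome assessment does speak of change, for self-management only: "To measure this change in self-management skills, we will measure perceived confidence in own self-management skills on a visual analogue scale".
- **Assessment of the outcomes** confirms that the baseline values are available in general: "The self-reported outcomes will be assessed at baseline and at 3, 6, 9 and 12 months of follow-up".
- **Covariate adjustment** appears only for the time-to-return-to-work outcomes. If baseline tests of prognostic characteristics are significant, "a Cox regression analysis will be performed including those prognostic parameters". Nothing comparable is said for the multilevel models.

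**The concern.** Improvement most naturally means change from baseline. If the baseline score is the first of the repeated outcomes and each arm has its own baseline mean, the arm-by-time contrast in complete data is the difference between arms in mean change. That contrast subtracts the whole baseline score, although a follow-up score regresses on baseline with a slope below one. Two costs follow. The intervals for the secondary effects, and for the test of the proposed mechanism, are wider than the data require. And an arm that happens to start higher is marked down too far.

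The adjustment rule the article does give would not help. It concerns Cox models only and is triggered by significance at baseline, so moderate chance differences would pass unnoticed.

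**Working it through.** **The plan's own figure.** Sample size gives 72 % versus 89 %, power 80 %, p < 0.05, 170 patients before loss. With a two-sided test, 1:1 allocation and pooled variance, the mean proportion is 0.805 and

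n per arm = [1.96 × √(2 × 0.805 × 0.195) + 0.8416 × √(0.72 × 0.28 + 0.89 × 0.11)]² / 0.17² = (1.098 + 0.461)² / 0.0289 = 84.1, so 85 per arm and 170 in total.

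Allowing for 10 % loss, 170/0.9 = 188.9, or 189 against the stated 190. The figure reproduces. It concerns the primary outcome; the article states no power or precision for the scores discussed here. I use 85 per arm below.

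**Inputs for the scores.** rho is the correlation between baseline and follow-up score. It is not in the document, so I assume 0.3 to 0.8, with equal SD at both times, one follow-up visit and effects in SD units.

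**Variance of the arm difference:**

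- follow-up score alone: 2/n
- change score: (2/n) × 2(1 − rho)
- baseline-adjusted: (2/n) × (1 − rho²)

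Change relative to adjusted: 2(1 − rho)/(1 − rho²) = 2/(1 + rho).
Follow-up alone relative to adjusted: 1/(1 − rho²).

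| rho | SE follow-up only | SE change | SE adjusted | change / adjusted variance | follow-up only / adjusted variance |
|---|---|---|---|---|---|
| 0.3 | 0.153 | 0.182 | 0.146 | 1.54 | 1.10 |
| 0.5 | 0.153 | 0.153 | 0.133 | 1.33 | 1.33 |
| 0.7 | 0.153 | 0.119 | 0.110 | 1.18 | 1.96 |
| 0.8 | 0.153 | 0.097 | 0.092 | 1.11 | 2.78 |

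At rho 0.5 the difference detectable with 80 % power is (1.96 + 0.8416) × 0.153 = 0.43 SD for the change score, against 2.80 × 0.133 = 0.37 SD with adjustment.

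The follow-up-only columns matter for self-management and self-efficacy, where the article speaks of differences on the scores and not of improvement. That reading loses precision as well, most when rho is high.

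**Chance imbalance.** Given a baseline difference D between arms, the change-score estimate is shifted by −(1 − rho) × D. For D = 0.2 SD at rho 0.5 this is −0.5 × 0.2 = −0.1 SD; at rho 0.8 it is −0.04 SD. The SE of a baseline difference is √(2/85) = 0.153 SD, so D = 0.2 SD has z = 0.2/0.153 = 1.30 and two-sided p of about 0.19. A difference at least this large arises by chance about one time in five per scale, and the planned baseline t test would not flag it.

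**The case against.** The strongest reply is that the article names a class of model and a question, not a full specification. It does not fix the dependent variable, the coding of time or the covariance structure, and a condensed article may leave model terms to a fuller plan. A model with baseline means constrained to be equal is itself a longitudinal multilevel analysis of improvement, so the published sentence does not exclude the better analysis. This stands as a limit on what can be claimed. It does not remove the point: the article addresses covariate adjustment in the same section, confines it to the Cox models, and words the multilevel comparison as improvement. Change from baseline is therefore the natural reading.

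A reader might infer more than the document supports:

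- *That baseline is ignored, or that the effects are biased.* A change score uses the baseline by subtraction, and over repeated randomisation its contrast is unbiased. The fault is over-correction and lost precision.
- *That all these outcomes are compared as improvement.* The analysis section for self-management and self-efficacy does not say so.
- *That the loss reaches 67 %.* That figure arises at rho 0.5 for the mean of the four follow-up visits: 0.625/0.375 = 1.67. It needs equal correlations between all visits and an effect averaged over visits, neither of which the plan specifies.
- *That every baseline score is already in hand.* The Abstract describes patients on sick leave, so scores for work limitations and quality of work life may not exist at baseline for some or many of them.

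**Conclusion.** The point holds as a free improvement to the analysis of the secondary and intermediate scores. On the natural reading, the single-visit variance exceeds that of a baseline-adjusted analysis by about 54 % at rho 0.3, falling to 11 % at rho 0.8. A chance baseline difference of 0.2 SD moves the effect by 0.1 SD at rho 0.5.

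These sizes rest on an assumed correlation, equal SDs, and a change-from-baseline contrast that the wording suggests but does not fully define. If the follow-up scores were instead compared without baseline, the excess would run from 10 % to 178 % over the same range, so the recommendation does not depend on which unadjusted reading is right. The primary relative risk and the sample size of 170/190 are untouched.

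**What to change.** In both statistical-analysis passages (secondary parameters; self-management and self-efficacy), state one of two models:

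1. The 3-, 6-, 9- and 12-month scores are modelled on arm, visit and arm-by-visit, with the outcome's own baseline score as a covariate.
2. Baseline is kept as one of the repeated outcomes, with arm means constrained to be equal at baseline.

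State that the choice applies whatever the baseline tests show. Apply it to work ability, SF-12, self-management and self-efficacy. Apply it to work limitations and quality of work life only where a baseline score exists for patients on sick leave, and say how those two outcomes are handled otherwise.

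The cost is a change of wording, with no extra patients, visits or questionnaires. Fixing the model now also removes the choice between change, follow-up-only and adjusted analyses once data have been seen.
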